### Intervention Delivery and Verification

Experimental group participants receive personalized recommendations explained by the researcher in person on day 30. Participants can clarify and provide feedback. A closure interview at day 60 verifies engagement and implementation attempts, and includes a subjective effectiveness assessment.

### Personalized Sleep Intervention Framework

The intervention content is based on individual ML feature importance ranking, and participants receive nonpharmacological recommendations from a predefined library (Multimedia Appendix 1) targeting their top 2‐4 predictive sleep parameters [108-116]. Example recommendations for TST optimization (if sleep_duration is a key predictor) are as follows: ensure wake-up time commitment for too much sleep and bedtime commitment for too little sleep. Example recommendations for sleep efficiency enhancement (if movement_awakening is a predictor) are as follows: use white noise, ensure a quiet environment, and restrict caffeine intake (avoid intake ≤6 hours before bedtime). Example recommendations for sleep timing regulation (if sleep_cycle is a predictor) are as follows: ensure a consistent sleep-wake schedule and keep the bedroom cool (around 18 °C‐20 °C).

Experimental group participants receive personalized recommendations, and the top 2‐4 recommendations are explained by the researcher during the in-person meeting. Adherence tracking involves self-reported compliance assessed at study closure (0%‐100% scale). Control group participants receive generic sleep hygiene education without personalization by the researcher during the in-person meeting.

### ML-Derived Heterogeneity by Design

Personalized interventions intentionally create between-participant variability within the experimental group, and this is the intervention’s defining feature, not a statistical flaw. Participant A might receive recommendations targeting REM sleep and sleep timing, while participant B might receive advice on deep sleep and wake episodes, based on individual ML model findings. This heterogeneity is the core innovation: targeting individual-specific parameters rather than universal protocols.

With regard to statistical implications, within-group variance in the experimental arm may exceed variance in the control arm. This reduces statistical power but reflects real-world personalization implementation. If personalization is effective, the increased precision of targeting individual needs should overcome variance increases. If personalization shows no benefit despite this heterogeneity, the approach is not superior to simpler generic advice. We do not attempt to statistically “control for” intervention heterogeneity, as it represents the intervention. Exploratory analyses will descriptively examine whether certain recommendation types (eg, duration-focused vs architecture-focused recommendations) show differential effectiveness, informing future research on personalization boundaries.

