### Trial Design

This is a parallel-group randomized controlled pilot trial with a 1:1 allocation ratio. Participants are stratified by sex (male/female) and randomized to either (1) a control group receiving generic sleep hygiene education or (2) an experimental group receiving personalized ML-derived behavioral recommendations.

The observation period is 60 days, which aligns with PSQI requirements for 30-day data collection periods. PSQI assessments are performed at (1) baseline (prior to device use), (2) day 30 (first monitoring period), and (3) day 60 (postintervention period). This enables subjective-objective correlation while establishing a baseline (days 1‐30) to be used as a covariate for intervention analysis (days 31‐60). While 30 days may be minimal for entrenching behavior change, this pilot will establish feasibility and preliminary effect sizes for future extended trials.

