### Sample Size: Pilot Feasibility Justification

This pilot trial enrolls 32 participants (16 per arm; stratified by sex), and this is consistent with established pilot study guidelines recommending 12‐15 participants per arm for feasibility assessment [117-120]. The sample size is explicitly designed for pilot objectives, not definitive efficacy testing.

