### Power Analysis Context: Not Designed for Definitive Testing

The sample size provides adequate power (>80%) only for very large effects (*d*≥1.0). For moderate effects typical in sleep research (*d*=0.3‐0.7), the power is insufficient, which is consistent with this study’s role as a feasibility-focused pilot trial. We explicitly acknowledge insufficient power for moderate effects. The power analysis table showing power for different effect sizes is presented in Multimedia Appendix 2. If moderate-to-large effects exist, we may detect a signal, and if effects are small, this pilot will yield null results, informing researchers that larger samples, longer interventions, or different approaches are needed. Both outcomes are valuable for the advancement of the field.

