### Statistical Methods

#### Primary Analysis: Single-Covariate Analysis of Covariance

The mean sleep score in the postintervention period (days 31‐60) is compared between groups using analysis of covariance with a single covariate: mean sleep score in the baseline period (days 1‐30).

$$Model:Postintervention\;score=\beta_{0}+\beta_{1}\;(group)+\beta_{2}\;(baseline\;score)+\epsilon$$

The control group is coded as “0,” and the experimental group is coded as “1.” The primary inference is based on the β₁ coefficient (group difference adjusted for baseline). The effect size is calculated as Cohen *d* with 95% CIs. Statistical significance is assessed at *α*=.05 (1-tailed per directional hypothesis), but the interpretation emphasizes the effect size magnitude and CI width, given the pilot nature of the study.

We do not use multiple covariates (age, sex beyond stratification, and behavioral factors) to avoid overfitting with the small sample size. Sex stratification in randomization addresses balance concerns without requiring covariate adjustment.

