### Interpretation Guidance

All findings will be interpreted as preliminary, hypothesis-generating signals requiring confirmation in adequately powered trials. We will report effect sizes, CIs, and descriptive patterns rather than definitive claims of efficacy or lack thereof. The pilot’s value lies in feasibility demonstration and effect size estimation for future sample size calculations, not in definitive answers about intervention effectiveness.

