Several important considerations frame the interpretation of the anticipated findings. The study acknowledges the inherent limitations of consumer wearable research, particularly reliance on Samsung’s proprietary sleep score algorithm. While this limits reproducibility of exact score computation and precludes independent PSG validation of the composite metric, the personalization framework itself is deliberately manufacturer-agnostic. Additional methodological constraints include the single-device focus, the limited geographic and cultural generalizability (Mexico City context with unique altitude, pollution, and lifestyle factors), potential measurement errors inherent to consumer-grade sensors, and the 30-day intervention period, which may be insufficient for sustained behavior change in entrenched sleep habits. The study excludes individuals with diagnosed sleep disorders, limiting the findings to healthy populations seeking sleep quality optimization rather than clinical treatment.

If validated through this pilot study, the methodology could direct sleep optimization from universal protocols toward individualized behavioral targeting, offering a scalable approach to sleep health improvement.

However, if the findings reveal no difference between personalized and generic interventions, there would be valuable evidence that (1) generic interventions may be equally effective and more cost-efficient for healthy populations, (2) the ML personalization approach requires refinement before clinical utility can be established, or (3) consumer wearables may not yet provide sufficient data quality for meaningful pattern detection at the individual level. Both positive and null findings will advance scientific understanding and inform future research directions.

The results will be available by March 2026 and will be disseminated through a peer-reviewed publication regardless of the findings (positive, null, or negative). A deidentified dataset will be part of the study output. This transparency supports scientific rigor and allows the broader research community to build upon the methodological framework regardless of this pilot’s specific outcomes.

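### The protocol gives conflicting readings of a null result, and two of them go beyond what 16 participants per arm can show

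*Protocol article*

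**What the plan says.** Two places tell the reader what a null result would mean for the approach itself:

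- Methods, ML-Derived Heterogeneity by Design: "If personalization shows no benefit despite this heterogeneity, the approach is not superior to simpler generic advice". The sentence carries no qualifier. Earlier in the same paragraph, the section accepts that the extra variance in the experimental arm lowers power.
- Discussion, Conclusions: a finding of no difference is described as useful evidence for one of three things. The first is that "generic interventions may be equally effective and more cost-efficient for healthy populations". The others are that the ML method needs more work, or that wearable data may not be good enough. Too small a sample is not on the list.

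Three places point the other way:

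- Power Analysis Context: "For moderate effects typical in sleep research", given as d=0.3 to 0.7, power is said to be insufficient. A null is said to call for more participants, a longer intervention or another approach.
- Interpretation Guidance: effect sizes, CIs and descriptive patterns are to be reported "rather than definitive claims of efficacy or lack thereof".
- Primary Analysis: the emphasis is placed on effect size and CI width.

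The article also states, under Exploratory Analyses, that it contains the whole statistical analysis plan and that there is no separate one. No other document is therefore expected to settle which reading applies.

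**The concern.** The heterogeneity sentence turns a failure to see a benefit into a property of the approach. That cannot be followed together with the power section, which says the trial is likely to miss moderate effects, or with Interpretation Guidance, which rules out firm claims of no efficacy. The Discussion item is milder, but it invites an equal-effectiveness message from a trial that gives no equivalence margin, and it leaves out the explanation the protocol concedes elsewhere. The cost-efficiency remark has no support in the trial: none of the listed outcomes measures cost, and cost-effectiveness is deferred to later research under Implications for Future Research.

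At stake is the published message from a null. If the two sentences were followed, low precision could be reported as evidence against personalization or in favour of generic advice, and a larger trial might be discouraged for the wrong reason.

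**Working it through.** **Inputs from the protocol.** 16 per arm (Sample Size); 1:1 allocation (Trial Design); "Statistical significance is assessed at *α*=.05", "1-tailed per directional hypothesis" (Primary Analysis); ANCOVA with the baseline mean score as the only covariate; moderate range d=0.3 to 0.7 (Power Analysis Context). Excluded participants are replaced, so 16 per arm is taken as evaluable.

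**Assumed.** The baseline-to-follow-up correlation r is not given, since the pilot is meant to estimate it. Values from 0 to 0.8 are shown. Equal variances are assumed, with d in units of the unadjusted SD.

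**Formulas.**
- Noncentrality = d/√(1−r²) × √(n/2), with √(16/2) = 2.828. Power comes from the noncentral t distribution, df 30 without the covariate and 29 with it.
- SE of the difference in SD units = √(2/16) × √(1−r²) = 0.354 × √(1−r²).
- Two-sided 95% CI half-width = t(0.975) × SE. Largest observed difference still non-significant one-sided = t(0.95) × SE.

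**The plan's own figure.** At d=1.0 and one-sided .05, power is 86.8% (t) or 88.2% (normal approximation). The stated power above 80% therefore reproduces. The one-sided t test reaches 80% at about d=0.90.

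**Results.**

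| | No covariate gain | r=0.5 | r=0.7 | r=0.8 |
|---|---|---|---|---|
| Power, d=0.3 | 21% | 25% | 31% | 40% |
| Power, d=0.5 | 40% | 48% | 61% | 74% |
| Power, d=0.7 | 61% | 72% | 86% | 94% |
| 95% CI half-width (SD) | 0.72 | 0.63 | 0.52 | 0.43 |
| Largest non-significant difference (SD) | 0.60 | 0.52 | 0.43 | 0.36 |

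Example without covariate gain: half-width = 2.042 × 0.354 = 0.72. At r=0.7: SE = 0.354 × √0.51 = 0.252, and half-width = 2.045 × 0.252 = 0.52.

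**Reading.** A true d=0.5 gives a non-significant result in 60% of such trials without covariate gain and in 39% at r=0.7. For d=0.3 the figures are 79% and 69%. Even with an observed difference of exactly zero, the CI contains d=0.3 at every r shown and d=0.5 for r up to 0.7. A null can also occur with a positive estimate. Without covariate gain, a difference just under 0.60 SD is non-significant, with an upper limit near 0.60 + 0.72 = 1.32 SD.

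**Equal effectiveness.** Take an equivalence margin of 0.5 SD, assumed because the protocol gives none. Two one-sided tests at .05 with 80% power, a true difference of zero and no covariate gain need 2 × ((1.645 + 1.282)/0.5)² ≈ 69 per arm. With 16 per arm the power of that procedure is about 0% for r=0 or 0.5, and 22% at r=0.7.

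**The case against.** A reader might infer that the plan will treat a null as proof that personalization fails or that the two kinds of advice are equivalent. The documents do not support that. The sections that govern analysis and reporting give the sound reading already: Primary Analysis stresses effect size and CI width, Interpretation Guidance calls every finding preliminary, and the power section says what a null would call for. The heterogeneity sentence sits in an intervention section, has no test or threshold attached, and could be meant only as superiority not being shown. The Discussion item is hedged and is one of three alternatives. It is not a definitive claim, so it does not breach Interpretation Guidance.

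A reader might also infer that a null is the most likely outcome throughout the moderate range. That fails at d=0.7 (power 61% even without covariate gain) and at d=0.5 with r=0.7 (again 61%).

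All of this stands, and it limits the point to an inconsistency. It does not remove it. The heterogeneity sentence as written asserts a fact about the approach, and the Discussion list still omits insufficient power, although the power section and Study Limitations both concede it.

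**Conclusion.** The point holds as a conflict between passages that should be reconciled. The unhedged sentence under ML-Derived Heterogeneity by Design contradicts both the power section and Interpretation Guidance. The Discussion item sits badly with the power section because it omits low power, and its cost-efficiency remark rests on nothing the trial measures.

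The statistical reason is firm at d=0.3 for every correlation examined, and at d=0.5 for correlations up to 0.7: a null, even with an estimate of zero, leaves such a benefit within the 95% CI. It weakens for stronger covariate gain. At r=0.8 a zero estimate would exclude d=0.5 (±0.43), and d=0.7 is already excluded at r=0.5 (±0.63). These figures rest on 16 evaluable participants per arm, equal variances and an assumed r. The protocol itself expects larger variance in the experimental arm and says this lowers power.

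No planned estimate, test or sample size is called into question here.

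**What to change.** 1. In ML-Derived Heterogeneity by Design, replace the sentence with one saying that, if no benefit is seen, superiority was not demonstrated and the result is inconclusive, to be reported with its two-sided 95% CI.
2. In the Discussion (Conclusions), add insufficient power to the explanations of a null. Drop the first item or qualify it, including the cost-efficiency remark, so that it agrees with the power section and Interpretation Guidance.

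No equivalence margin is needed for this pilot. If equivalence were ever claimed, both CI limits would have to lie inside a margin; an upper limit alone could at most rule out a benefit beyond it. Such a margin would have to be fixed before outcome analysis. Fixing it before unblinding is not a usable rule, because the researcher learns the allocation at day 30 in order to deliver the recommendations.

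The cost is wording only. Conduct and analysis stay the same, and the conclusion drawn from a null becomes less strong.

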### Intervention Modifications

No modifications to assigned interventions are permitted during the 60-day study period. If participants cannot implement specific recommendations due to unforeseen circumstances, this is documented as nonadherence rather than modification. Adherence tracking captures whether participants attempted to follow recommendations, not whether recommendations were modified.

### Concomitant Care Protocol

The aspects related to the concomitant care protocol are as follows:

Permitted: regular medical care, stable chronic disease management, and emergency careProhibited: new sleep medications, sleep clinic consultations, or other sleep apps or programsDocumentation: weekly medication diary and immediate reporting of treatment changesSafety: participants with sleep deterioration (<30 score for >1 week) withdrawn and referredBaseline: usual care patterns documented at enrollment

### Adherence Assessment

In the experimental group, adherence to personalized recommendations is assessed through self-report at the day 60 closure interview. Participants rate adherence on a scale from 0% to 100% for each recommendation provided. In the control group, adherence to generic sleep hygiene is assessed in a similar manner. Device wear adherence is monitored through objective data. Participants with missing data for >20% of nights may be excluded and replaced.

### Outcomes

#### Primary Outcome: Mean Samsung Galaxy Watch 4 Sleep Score During the Postintervention Period

We are working within proprietary constraints. We use the Samsung sleep score (1-100 scale) as the primary outcome for the following reasons: (1) real-world relevance: the score is the metric users see and seek to optimize in consumer wearable ecosystems; (2) continuous sensitivity: the scoring scale (1‐100) detects individual-level changes with precision, which categorical systems cannot achieve; (3) composite integration: the score algorithmically combines multiple sleep dimensions (duration, architecture, efficiency, and fragmentation), providing a holistic optimization target; (4) feasibility for personalization: continuous data for 60 nights enable individual ML models to identify predictive patterns; and (5) validation through correlation: secondary PSQI outcomes confirm that objective score improvements correspond to subjective sleep quality perception.

There are some limitations. The use of a proprietary algorithm limits the reproducibility of exact score computation. Moreover, there is no PSG validation of the composite score specifically (though component parameters are validated [36-43]). Furthermore, the manufacturer-specific metric precludes direct cross-device comparisons. These limitations are inherent to consumer wearable research and do not invalidate the personalization methodology (they contextualize the interpretation). Our framework is designed to work *within* these pragmatic constraints while remaining transferable to other manufacturers’ proprietary systems.

#### Secondary Outcome: PSQI Global Score Measured at Three Time Points

The PSQI (0-21 scale) validates that objective sleep score improvements correspond to the subjective perception of sleep quality and functional impact, ensuring clinical relevance from the patient perspective. The PSQI is not used as a competing primary measure but rather as a tool to provide complementary validation that device-measured changes reflect meaningful improvements in lived experience.

### Measurement Time Points

The measurement time points are as follows:

Baseline (day 0): PSQIDays 1-30 (baseline period): continuous Samsung score collection for ML model training and baseline covariate establishmentDay 30: PSQI; intervention delivery of personalized behavioral recommendations to the experimental group or intervention delivery of standardized sleep hygiene education covering general recommendations applicable to all adultsDays 31‐60 (postintervention period): continuous Samsung score collection for the primary outcomeDay 60: PSQI; closure interview

### Exploratory Outcomes

The exploratory outcomes include (1) individual sleep parameter changes (which specific variables improve), (2) adherence to personalized recommendations (self-reported 0%‐100% scale), and (3) behavioral confounders (alcohol consumption, exercise, and stress documented in the closure interview).

### Participant Timeline

The measurement time points after eligibility screening, informed consent approval, and randomization in the control and experimental groups are presented in Figures1  2, respectively.

**Figure 1. F1:**
[figure not shown]
Illustration of the key actions during the 60-day study period in the control group. PSQI: Pittsburgh Sleep Quality Index.

**Figure 2. F2:**
[figure not shown]
Illustration of key actions during the 60-day study period in the experimental group. PSQI: Pittsburgh Sleep Quality Index.

### Sample Size: Pilot Feasibility Justification

This pilot trial enrolls 32 participants (16 per arm; stratified by sex), and this is consistent with established pilot study guidelines recommending 12‐15 participants per arm for feasibility assessment [117-120]. The sample size is explicitly designed for pilot objectives, not definitive efficacy testing.

### Pilot Objectives

The pilot objectives are as follows:

Feasibility: Can we successfully recruit, enroll, randomize, and retain participants? Can personalized ML interventions be delivered? Do participants engage with recommendations?Preliminary effect size estimation: What magnitude of difference between groups might we observe? What variability exists within groups? What baseline-to-follow-up correlation informs covariate adjustment? The estimates can inform future randomized controlled trial (RCT) sample size calculations.Methodology refinement: What challenges arise in data collection, ML model training, and intervention delivery? What proportion of nights yield usable data? Which sleep parameters show the most predictive value?Hypothesis generation: Does personalization show a promising signal warranting a larger trial? Do certain participant subgroups respond better?

### Power Analysis Context: Not Designed for Definitive Testing

The sample size provides adequate power (>80%) only for very large effects (*d*≥1.0). For moderate effects typical in sleep research (*d*=0.3‐0.7), the power is insufficient, which is consistent with this study’s role as a feasibility-focused pilot trial. We explicitly acknowledge insufficient power for moderate effects. The power analysis table showing power for different effect sizes is presented in Multimedia Appendix 2. If moderate-to-large effects exist, we may detect a signal, and if effects are small, this pilot will yield null results, informing researchers that larger samples, longer interventions, or different approaches are needed. Both outcomes are valuable for the advancement of the field.

